### Comparator

During the control period, older adults receive the usual care by staff at each participating nursing home (cluster), which is identical to the usual practice. While “the usual practice” may not be identical across homes, care staff generally do some resident assessments, though neither CGA with decision support nor CGA results- (evidence-)based ICCs tend to be conducted in a systematic way. CP is often neither individualized nor documented properly. The participation of older residents and/or their family members in the care planning process is very limited. The execution of care plans is left to the discretion of care staff of each home, following their existing practice patterns. Any other concomitant care or interventions that may affect trial outcomes are not permitted in the participating nursing homes during the current trial.

### Outcomes

Quality of care is the primary outcome, and several secondary outcomes including quality of life will be measured. We have also included process measures and staff-/organization-related measures as complementary. All outcomes and their measurement plans are summarized in Table 2, except the process evaluation measures, which are in Table 3.

**Table 2 Tab2:** Overview of the outcome variables, measures, and observation points

Variable	Data Source/Instrument	Measurement Points	Unit of Analysis
Primary Outcomes			
Quality of Care	interRAI LTCF quality measures (composite score)	T0 (baseline), T1, T2, T3	Resident
Secondary Outcomes: Patient-Related			
Quality of Care	interRAI LTCF quality measures (individual score)	T0 (baseline), T1, T2, T3	Resident
Care Needs	Number of triggered clinical action points of interRAI LTCF	T0 (baseline), T1, T2, T3	Resident
Functional Health	Bathel index; Mini-Mental Status Examination; Patient Health Questionnaire	T0 (baseline), T1, T2, T3	Resident
Quality of Life	EuroQol(EQ)-5; interRAI HRQoL; interRAI self-reported QoL (SQoL)	T0 (baseline), T1, T2, T3; T1 & T3 (SQoL)	Resident
Patient Satisfaction	Client Satisfaction Questionnaire	T1 & T3	Resident
Health Care Utilization	Hospital admissions; emergency department visits	Every three months	Resident
Costs	Questionnaire on the cost; direct and indirect costs	Every three months	Resident
Other Outcomes: Care Staff/Organization-Related			
Empowerment	Psychological Empowerment Instrument	T1 & T3	Nursing Home
Communication Satisfaction	Communication Satisfaction Questionnaire	T1 & T3	Nursing Home
Organizational Commitment	Organizational Commitment Questionnaire	T1 & T3	Nursing Home
Job Satisfaction	Job Satisfaction Scale	T1 & T3	Nursing Home
Technology/Innovation Acceptance	Modified Technology Acceptance Model Questionnaire	T1 + 1 month & T3	Nursing Home

**Table 3 Tab3:** Process evaluation on intervention and implementation strategies

Topic	Data Source/Analysis	Measurement Points	Unit of Analysis
Recruitment of cluster	[Qualitative analysis] - Measurement from documentation of recruitment & allocation process by research team	During recruitment of clusters	Nursing home
Delivery to clusters	[Quantitative analysis] - Measurement of intervention fidelity across its components: in-service training; care planning; case conferences with assistant & case conferences without support; coordination of care; supporting & tracking through ICT	During and after each component	Nursing home & Resident
	- Measurement of receipt in target population from the cloud-based SPEC computerized system	T2, T3	Resident
	[Qualitative analysis] - Measurement from interviews with onsite SPEC coordinators in charge of case management about what intervention is delivered and why	After T3	Nursing home
Response of clusters	[Quantitative analysis] - Measurement of standardized questionnaire items sent to participants along with other follow-up measurements	After T3	Nursing home
	[Qualitative analysis] - Measurement from documents and interview data about target population’s experience of and response to the intervention.	During and after each component	Nursing home
Recruitment and reach-in of individuals	[Quantitative analysis] - Measurement from documents and participant list	T0	
	- Quantitative comparison of those receiving vs. not receiving the intervention	T0, T1, T2, T3	Nursing home & Resident
	[Qualitative analysis] - Measurement from interviews with those who recruited the participants	During and after each component	Nursing home & Resident
Response of individuals	[Quantitative analysis] - Measurement from standardized questionnaire of individuals’ perceptions of the intervention and uptake of trial components. (TAM, questionnaire for process evaluation)	T1 + 1 month; after T3	Nursing home
	[Qualitative analysis] - Measurement from observational and interview data about target population’s experience of and response to the intervention (documents, web data, telephone calls, audiotape of case conferences, etc.)	During and after each component	Nursing home
Context	[Quantitative analysis] - Measurement from project manager’s documents and from standardized questionnaire to assess organizational and structural characteristics of nursing home	Before T1; after T3	Nursing home
	[Qualitative analysis] - Measurement from policy documents or interviews (semi-structured interviews to assess “care as usual” at baseline and at end of study)	Before T1; during and after each component; after T3	Nursing home
Implementation strategies	[Quantitative analysis] - Measurement of quantitative data from web and documents	During and after each component	Nursing home
	[Qualitative analysis] - Measurement from project manager’s documents and interview data about target population’s experience of and response to the facilitation strategies	During and after each component	Nursing home

#### Primary outcome measure

The primary outcome measure of the study is *quality of care* (*QoC*)*,* measured by a composite score of quality indicators (QIs) in the interRAI LTCF, which has good psychometric properties [23], similar to the primary outcome measures of the MIC intervention in resident care facilities in the Netherlands [14] and the European Services and Health for Elderly in Long-TERm Care (SHELTER) study [24]. The outcomes will be measured four times: at T0 (baseline), T1 (3 months; the end of observation period), T2 (6 months; 3 months after the beginning of the intervention), and T3 (9 months; the end of the intervention, 6 months after its start). Resident outcome data will basically be collected every three months by external nurse assessors trained by the SPEC research team.

#### Secondary outcome measures

*QoC*, measured by individual interRAI QIs, is a secondary outcome measure to observe the effects of the SPEC intervention on quality in various health and function domains separately, assuming the impact of the program may not be the same across the domains.

*The extent of care needs* is measured with the number of total triggered CAPs in four categories: functional performance, cognition/mental health, social life, and clinical issues [19]. We will examine the change in the number before and after the program implementation. Some CAPs may have too low a prevalence in Korean nursing homes, which would threaten their validity, so we will remove them from the final set of CAPs for the analysis.

*Functional health* will be measured by three measures (the Modified Bathel index, Mini-Mental Status Examination, Patient Health Questionnaire). The Bathel index is used to measure performance of physical functions in activities of daily living. We will adopt the modified version by Shah et al. [25], which has demonstrated high inter-rater reliability (0.95) and test–retest reliability (0.89) as well as high correlations (0.74–0.8) with other measures of physical disability [26]. The Mini-Mental Status Examination (MMSE) [27] is used to measure cognitive impairment using a 30-point questionnaire. The Korean version of MMSE (K-MMSE) has good sensitivity (0.70-0.83) and convergent validity (0.78) [28]. The PHQ-9 is a depression module of the PHQ (Patient Health Questionnaire) developed by Spitzer et al. [29] and translated into Korean by Han et al. [30]. The Korean version of the PHQ-9 has good internal consistency (0.88) and convergent validity (0.74).

The *quality of life* (QoL) of older nursing home residents will be measured with the Korean version of the EQ-5D-5 L. The EQ-5D, developed by EuroQol Group, is a measure of health-related QoL that has five items, and each item measures different dimensions of health–-mobility, self-care, usual activities, pain/discomfort, and anxiety/depression [31]. The EQ-5D-5 L will be adopted because 5 L is known for having better sensitivity and a lower ceiling effect than other versions of EQ-5D in Korea [32]. General QoL of residents will be measured with the interRAI Self-Reported QoL (interRAI SQoL) [33].

*Patient satisfaction* will be measured with the K-CSQ (Korean Client Satisfaction Questionnaire) [34]. The original CSQ developed by Larsen et al. [35] has six different forms, and CSQ-8, consisting of 8 items, is most widely used in consumer or client satisfaction studies. The K-CSQ by Kim et al. [34] is a translated and modified version of CSQ-8 to measure the satisfaction of nursing home residents in Korea; good psychometric properties have been reported.

As for *health care utilization*, costs will be collected from a societal perspective and consist of medical costs and intervention costs. Medical costs will be calculated by multiplying the healthcare utilization and unit costs. Other healthcare utilization data includes the number of physician visits, length of stay, service use in the facilities, and time consumption. Nationally representative data—such as the National Health Insurance database [36] and Korea Health Panel Survey data [37]—will be used to calculate the unit costs. Intervention costs that occur while operating the SPEC program will also be calculated. Productivity costs are to be excluded, taking into account the old age and frail health status of the residents.

#### Other measures: Staff-level & organization-related measures

Other outcome measures include care staff-level and organization-related measures, for which participating nursing staff members will directly answer a set of survey questionnaires.

*Empowerment* of the nursing home staff members will be measured with the Psychological Empowerment Instrument (PEI), which was developed by Spreizer [38] and translated into Korean and modified by Ahn [39]. The PEI is composed of 4 domains (meaning, competence, self-determination, impact), and each domain has 3 items for a total of 12 items. The original instrument’s 7-point scale was modified into 5-point scale by Ahn [39], and its Cronbach’s α was 0.898.

*Communication satisfacti*on will be measured with the Communication Satisfaction Questionnaire (CSQ) developed by Downs & Hazen [40], translated into Korean and modified by Lee [41], and optimized to be used in health care settings by Park [42]. In Lee’s study [41], the original 40 items (8 domains, 5 items in each domain) of the instrument were modified into 24 items (3 items for each of the 8 domains).

*Organizational commitment* refers to employees’ identification with and attitudes toward the organization they are affiliated at, and also strength of involvement and relationship with the organization [43], which will be measured by the 15-item Organizational Commitment Questionnaire (OCQ) that was developed by Mowday et al. [43] This study has adopted the OCQ as translated and modified by Park [44] for use at long-term care settings in Korea.

*Job satisfaction* is measured with the 20 items on the self-rated Korean Minnesota Satisfaction Questionnaire (K-MSQ) [45] to measure organizational commitment, which was a modified version of Park’s [46] translation of the short version of the MSQ [47]. The K-MSQ [45] is a version of the MSQ applied to health care settings; Cronbach’s α for the instrument was 0.795 for the extrinsic factors, 0.862 for the intrinsic factors, and 0.908 for the general factors.

*Technology acceptance* will be measured with the TAM questionnaire, which was developed based on the Technology Acceptance Model [48]. The original TAM is a 10-item, self-rated questionnaire using a 7-point Likert scale, and it consists of 4 domains as follows: behavioral intention, perceived usefulness, perceived ease of use, and subjective norm. No existing TAM questionnaire in Korean is relevant for nursing home settings in Korea, so we translated and modified the TAM for this study and pre-tested the instrument, which resulted in good reliability.

#### Process measures

It is challenging to evaluate a complex intervention like the SPEC, as the intervention itself combines various components into an integrated program. Thus, each component is distinct and independent, but at the same time, somewhat interconnected. In addition, the intervention is not implemented in a vacuum, but situated in the unique context in which the intervention is delivered [49, 50]. Thus, process evaluation is invaluable for understanding the background, integrated process, and results, and also can give insights into applying the same intervention to a different setting in the future [49]. The process evaluation will use a mixed methods design, in which quantitative and qualitative data will be collected using standardized questionnaires, case studies, and focus group interviews guided by open-ended questions. The data will cover the following topics: the process of recruiting the nursing homes, delivery of the intended program (interventions), responses of participating homes to the program, recruitment of and outreach to actual resident participants in each home, response of individuals, context of program delivery, and implementation strategies (Table 3).

### Sample size & recruitment

Sample size was calculated using the formula for incomplete stepped-wedge CRT designs [11]. The primary outcome of the trial is quality of care (composite score of QIs of the interRAI LTCF), and the expected intervention effects (proportion 1: 0.115, proportion 2: 0.182) were determined based on a study by Boorsma et al. [9], a similar intervention study. The ICC was also set to be identical to Boorsma et al.’s [9], which was 0.01. Unlike Boorsma, however, we modified the correlation matrix V of Hemming et al.’s [11] formula in two ways. First, in order to take into account that the primary outcome will be measured repeatedly on the same residents, we added a resident-specific random effect in the calculation of the correlation matrix; we assumed the correlation coefficient was 0.25 based on the ratio between the ICC and correlation coefficient used in Mutinga et al. [51]. Second, we also accounted for the fact that some QIs included in the composite QI score for the primary outcome were measured as the difference between two successive time points for the same individual in the same cluster. The calculation was done using R 3.2.4., assuming a total of 10 clusters where 2 clusters are randomized at each step.

Based on the power calculation, the required minimum cluster size for detecting the expected intervention effect on the primary outcome with an 80% power under alpha = 0.05 is *n* = 45. (If the outcome is measured separately at each time point, *n* = 33.) We aimed to recruit nursing homes with at least 67 beds based on two assumptions: that about 80% of residents in a public LTCI-certified nursing home in Korea would meet our trial inclusion criteria and agree to participate, and also that about 15% of the recruited older residents would drop over the course of our trial. These assumptions were based on our earlier national nursing home survey study [52] and also publicly available data on the characteristics of LTC residents [53].

In order to promote recruitment, the participating nursing homes were recruited between March and April, 2015. In-person information sessions organized by the PI and key research team members were held multiple times at a convenient time and place for nursing home administrators and staff members who showed interest in study participation for quality improvement purposes. The SPEC program is an institution-level intervention for quality improvement purposes, so we offer it to all older residents in participating homes who meet our recruitment criteria; and if they agree to participate, informed consent is obtained after a detailed explanation of the study. We allow new enrollments when an older adult is newly admitted in a participating nursing home and (s)he meets our trial criteria. New enrollments mainly occur when existing participants drop due to discharge or are transferred to other institutions or communities, etc., due to the high occupancy rate of participating homes. The new enrollment is not only for recruitment purposes but also for a practical purpose: the participating homes would like to assess and provide care management for their newly admitted residents.

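### On the protocol's own inputs, 33 residents per home gives about 72% power rather than 80%; the headline 45 may share the fault, but the article does not settle it

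*Protocol article*

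**What the plan says.** All of this stands in the Protocol article, section Sample size & recruitment, unless another section is named.

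- Method: "Sample size was calculated using the formula for incomplete stepped-wedge CRT designs", with the covariance matrix V changed in two ways: a resident-level random effect was added, and allowance was made for quality indicators that are differences between successive visits.
- Effect: "proportion 1: 0.115, proportion 2: 0.182". The section does not say which is the control value.
- Intracluster correlation: taken from a similar earlier trial, "which was 0.01".
- Repeated measurement: "we assumed the correlation coefficient was 0.25".
- Layout: "assuming a total of 10 clusters where 2 clusters are randomized at each step". Study design adds four measurements per home and a roll-out every three months. Primary outcome measure places T0 and T1 before the intervention and T2 and T3 after its start.
- Result: 45 per home is the "required minimum cluster size for detecting the expected intervention effect on the primary outcome with an 80% power under alpha = 0.05". The condition "If the outcome is measured separately at each time point" lowers this to 33.
- Recruitment: at least 67 beds, allowing for 80% eligible and consenting and 15% loss.

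The sample-size section does not say whether alpha is one- or two-sided, or which variance was used for the binary outcome. Effect evaluation fixes two-sided tests at 0.05.

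**The concern.** A binary outcome has a different variance at each of the two proportions. Under the planning alternative, half of each home's four measurements are made at 0.115 and half at 0.182. If the smaller variance is used for all of them, the standard error is too small and the power too high. The figure for 33 can be checked directly, because every input it needs is printed.

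At stake is the power statement for the primary outcome. If true power is near 72%, the chance of missing the planned effect is about 28%, not 20%, and a null result would be read against a power that the trial does not have.

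**Working it through.** **Inputs.** Difference 0.182 − 0.115 = 0.067. Home-level correlation 0.01. Within-resident correlation 0.25, taken as 0.01 + 0.24. Five sequences of two homes. Each home is seen in four consecutive quarters with states 0, 0, 1, 1. Five start points three months apart and four visits give 5 + 4 − 1 = 8 calendar quarters. Test: two-sided 0.05.

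**Formula.** Generalised least squares on home-by-quarter means, with a fixed effect for each quarter. For m residents per home, the covariance of a home's means at visits j and k is

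σ² × [0.01 + (0.24 + 0.75 × 1(j = k)) / m].

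For condition-specific variances, σ² is replaced by σ_j σ_k. The variance of the intervention effect is its diagonal element in (Σ X′V⁻¹X)⁻¹. Power = Φ(0.067/SE − 1.96).

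**Variances.**

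- At 0.115: 0.115 × 0.885 = 0.1018.
- At 0.182: 0.182 × 0.818 = 0.1489, which is 1.46 times as large.
- Average of the two: 0.1253.
- Pooled proportion 0.1485: 0.1485 × 0.8515 = 0.1264.

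**Check of 33 (four visits, separate measurements).**

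| Variance used | Needed per home | Power at 33 |
|---|---|---|
| 0.1018 everywhere | 33 (32 gives 79.6%) | 80.6% |
| Average, 0.1253 | 42 | 72.0% |
| Pooled, 0.1264 | 43 | 71.6% |
| Condition-specific | 43 | 71.8% |
| 0.1489 everywhere | 52 | 64.6% |

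The first row reproduces the printed 33. There SE = 0.02374, 0.067/0.02374 = 2.82, and Φ(2.82 − 1.96) = 0.806. With the average variance, SE = 0.02374 × √(0.1253/0.1018) = 0.02634, 0.067/0.02634 = 2.54, and Φ(2.54 − 1.96) = 0.72. The condition-specific result is the same whichever proportion is control. Treating 0.25 as additional to the 0.01 leaves 33 unchanged and moves the other requirements by at most one resident. Holding the home-level variance at its value for 0.115 raises the average-variance power only to 73.4%.

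**Check of 45 (successive differences).** The article does not give the modified V, so several structures were tried, using the differences at T1 to T3 unless noted.

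| Structure | Needed with 0.1018 | Needed with both proportions | Power at 45 with both |
|---|---|---|---|
| Lag-1 correlation −0.25, home correlation kept | 45 (80.2%) | 55 to 62 | about 70% to 74% |
| Lag-1 correlation −0.5, home correlation kept (both-proportion results with 0.115 as control) | 46 (79.9% at 45) | 56 to 60 | 70.9% to 73.6% |
| As the row above, resident effect also kept | 41 | 50 to 53 | 75% to 77% |
| T1 to T3 as levels, correlation 0.25 (average or pooled variance) | 36 | 46 to 47 | 79% to 80% |
| Differences with the home effect cancelled (average or pooled variance) | 35 to 37 | 43 to 45 | about 80% |

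In the first row, the low end (62 needed, 69.5%) applies if control is 0.182 and the high end (55 needed, 73.5%) if control is 0.115.

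**One-sided alternative.** One-sided 0.05 with average or pooled variance needs 32 for separate measurements. It needs 44 for differences with the home correlation kept. Each is one below the printed figure. At two-sided 0.05 the same calculations give about 72% power at 33 and about 71% at 45.

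**Bed target.** 45/0.85/0.80 = 66.2, hence 67. It follows from 45, not from 33.

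**The case against.** The strongest objection concerns the headline figure. A reader might infer that 45 was also built on the lower variance and that the trial's power is therefore 70% to 74%. The documents do not establish this. The article says only that some indicators are differences; it gives neither the correlation between them nor their share of the composite. A home effect that is constant over time cancels in a difference, and without it 45 is reached with both proportions and about 80% power. That 0.1018 with a lag-1 correlation of −0.25 returns exactly 45 makes a shared cause plausible, since one variance then explains both figures. It is no proof: −0.25 is nowhere stated, and sound variances also reach 45.

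The cause is likewise inferred. The article never says that the lower variance was used, and the one-sided route comes within one resident of both figures. That route would conflict with the two-sided test in Effect evaluation and leaves the same shortfall, so it changes the explanation and not the result.

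It is also true that 33 is a comparison figure on which recruitment does not depend. If the outcome were measured separately, the 45 actually used would give about 82% power with both proportions. New residents may also be enrolled when others leave, so the analysable number may exceed 45. These points limit the consequence. They do not make the printed 33 follow from its inputs.

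**Conclusion.** The point holds for 33. On the stated inputs with a two-sided 0.05 test, 80% power needs 42 to 43 residents per home, and 33 gives about 72%. This rests on the standard stepped-wedge model with fixed quarter effects and home and resident random effects, and on no unstated covariance.

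For 45, the conclusion is that it may share the fault. Power is about 70% to 74% if the same variance was applied to successive differences with the home correlation kept, and about 80% with both proportions under other structures. The supportable range is about 70% to 80%. That a condensed article omits V is not itself a fault; it only means that the 45 cannot be confirmed or refuted here. The planned analysis and its estimates are unaffected.

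**What to change.** Recompute both figures at two-sided 0.05, using p(1 − p) at the control proportion in control cells and at the intervention proportion in intervention cells, with the V matrix that the sponsor actually used. State which proportion is control, the variance rule and the sidedness.

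Then correct the statement for 33: either 42 to 43 are needed, or 33 gives about 72% power. Restate the power, or the detectable difference, at 45 and at the number of residents per home actually enrolled. Do not print 72% for 45 unless the sponsor's own V gives it.

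The cost is one revised paragraph and possibly a less favourable stated power. Trial status says that all ten homes have been rolled out and analysis has not begun, so the correction can still precede the results. No change to enrolment is needed.
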